### Residential immersive life skills (RILS) programs

RILS programs are a unique type of life skills program for youth with disabilities and provide opportunities for learning with peers in a university or college residence, for periods between one and three weeks. RILS programs use flexible, multi-faceted approaches to provide experiences in choice-making, facilitated goal-setting, trial and error learning, and risk taking [22]. RILS programs appear to provide opportunities for ‘situated learning’, a powerful educational approach where learning occurs within the environments where the skills will be needed [23], which increases their potential to provide sustainable gains. Expert service providers report intentionally creating a safe, supportive, and engaging environment at RILS programs and tailoring learning strategies to the needs of the youth [24]. Non-intrusive strategies are common, such as allowing youth to ‘fail safely’, thus experiencing the consequences of their decisions in a supported environment. This can result in feelings of empowerment and self-determination [24].

The residential nature of RILS programs offers repeated opportunities to master skills and also allows youth to learn skills as part of their everyday life, termed ‘experiential learning’ [25]. RILS programs also facilitate interactions with peers with disabilities, offering intense learning and social experiences that go beyond skill development [26]. For some participants, this is one of their first opportunities to engage with others with disabilities, which may lead to greater understanding of their identity [27]. RILS programs often result in profound changes in young people and have been described as a ‘turning point’ in their transition to adulthood [28]. Secondary benefits may also arise: Service providers report their own clinical practice to be positively impacted by spending extended time with the youth and witnessing their daily reality, while parents often experience a transformation in their hopes and expectations for their child’s future [28].

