### Settings and intervention

Three core organizations in the province of Ontario, Canada, deliver well-established RILS programs. Program coordinators from these three organizations have collaborated for over 10 years to develop the programs and thus they share common goals and a common philosophy.

The programs run once per year over the summer. Each is delivered by a team of service providers, including occupational and physical therapists, therapeutic recreation specialists, life skills facilitators, nurses, social workers, and personal attendants. All programs take place in a university or college residence for periods of one to three weeks.

Although self-determination theory was not explicitly used in the initial design of the RILS programs, repeated opportunities for youth to make decisions and to practice daily tasks (e.g., budgeting, laundry, directing personal care, cooking, navigation, meal planning) aim to promote the development of self-determination and self-efficacy.

To participate in the programs, youth must have a child-onset disability, the cognitive capacity to set goals, and must not have behavioural issues that would interfere with their ability to participate in a group learning experience. Youth with mild cognitive impairments, as assessed by clinicians, are eligible to participate. The age range for participation in the programs is 14 to 21 years. Past participants in the three RILS programs have had diagnoses of cerebral palsy (50 %), spina bifida (15 %), acquired brain injury (5 %), communication disorders (5 %), as well as other conditions (25 %).

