### Research participants

Participants will be enrolled in four groups, with new participants recruited each year for three successive years. For practical and ethical reasons, we cannot randomly assign youth to treatment and control conditions.

Group A will consist of participants drawn from the youth enrolled in the three RILS programs. All youth will be English speaking, as this is the language of instruction of the RILS programs. In addition to meeting the eligibility requirements for program participation, as described above, youth who wish to participate in the research project will be screened separately by the research coordinator for their capacity to provide informed consent to participate in the study. Parents of youth in Group A must be English speaking to participate in interviews.

Group B will consist of youth who apply and are eligible to participate in one of the RILS programs but who are placed on a ‘deferred’ list to attend the program in the following year. This can be for a number of reasons, including numbers of places available and demand, extent of care needs, and youth availability. This group is intended to control for the motivation participants have for taking part in a RILS program.

Group C will consist of youth taking part in a group life skills program that is not residential. Several life skills programs at treatment centres in Ontario run over multiple days/weeks and employ a group format without being residential. This group will allow us to examine the relative effect of the immersive component of the RILS programs.

Group D, the control group, will consist of clients who are not participating in any group life skills program but are registered with one of six Ontario children’s treatment centres (the three core centres offering RILS programs, plus three additional collaborating centres).

Youth in the three comparison groups (Groups B, C, and D) must meet the eligibility criteria for the RILS programs, to ensure comparability with Group A. They will be matched to the RILS group in terms of age, gender, and diagnosis.

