#### Statistical power

We will recruit 30 youth in each of the four study groups in each of the 3 years of recruitment. This will result in a total of 90 youth participants per group. We have allowed for a liberal attrition rate of one-third, which will yield a minimum enrolment of 60 youth per group, sufficient for all analyses. A sample of 50 participants in each group will provide adequate power to detect moderate effect sizes (d = 0.50) on the primary outcome of self-determination, based on the following assumptions: power = 0.80, β = 0.20, α = 0.05 (one-tailed) [39]. Therefore, our projected sample of 60 youth will be sufficient to show any statistically significant changes in outcomes.

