### Data analysis

#### Quantitative analysis

Data from the online instruments (SDS and GSE) will be downloaded into an Excel spreadsheet. Data collection for the SPS-C, MEQAS, and SEAS will use hard copies of the instruments, with data entered into the Excel spreadsheet for data management. The Excel file will then be imported into SPSS for analysis. A portion of the data will be double entered to check for accuracy. The data from the two outcome measures (SDS and GSE) will be analysed descriptively to report means and standard deviations, pre, post, and at both follow-ups (3 and 12 months). The amount of change in the outcomes will be determined across the data collection time points. Baseline (pre-program) scores of all groups will be compared using t-tests to determine whether there are significant differences between groups on the dependent variables. Attrition rates for the groups will be calculated, to determine whether differential attrition is an issue. The RILS group (Group A) will be tested against one comparison group (Groups B, C or D) in each analysis. The primary analysis will therefore be a series of two between (study groups) and three within (longitudinal measurement points) repeated measures analyses of covariance (ANCOVAs), controlling for baseline scores, with the outcome measures as the dependent variables. Effect sizes will be calculated based on difference in pre- to post-test means, using Cohen’s D, with effect sizes between 0.30 and 0.50 considered medium and those >0.60 considered large [42]. We will use multilevel modeling to assess the proportion of variance in our outcome measures associated with the three program sites.

We will describe RILS program features by calculating means and standard deviations of the MEQAS scores and examining patterns of strategy use in the SPS-C data. The SEAS data for individual youth will be collapsed within each activity setting to provide an aggregate activity profile. We will examine convergence and correspondence between the SEAS and the SPS-C and/or MEQAS. Our previous pilot work demonstrated convergence between scores on the MEQAS (observable program features) and SPS-C (observable service provider strategies) [29]. Scores on the SEAS were also further enhanced by youth-reported experiences captured during brief interviews. These initial indicators of conceptual congruence will be further explored during this study.

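### The primary ANCOVAs and the sample size ignore that the residential program (and Group C) is delivered in groups; the separate three-site variance share does not correct this

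*Protocol article*

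**What the plan says.** Delivery of the residential program, in the protocol article:

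- Settings and intervention: "Three core organizations in the province of Ontario, Canada, deliver well-established RILS programs", and "The programs run once per year over the summer".
- Research participants: "Participants will be enrolled in four groups, with new participants recruited each year for three successive years".
- Residential immersive life skills (RILS) programs: the programs "provide opportunities for learning with peers in a university or college residence, for periods between one and three weeks". The same section counts contact among participants as part of what is offered: "RILS programs also facilitate interactions with peers with disabilities, offering intense learning and social experiences that go beyond skill development".

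Group C is group-delivered too (Research participants): "Several life skills programs at treatment centres in Ontario run over multiple days/weeks and employ a group format without being residential". The number of such programs is not given.

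Analysis (Quantitative analysis): Group A is tested against one comparison group at a time in repeated measures ANCOVAs, two groups by three post-baseline time points, with the baseline score as covariate. No term for site, year or peer group is described. The only multilevel step is "We will use multilevel modeling to assess the proportion of variance in our outcome measures associated with the three program sites".

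Sample size (Statistical power): "A sample of 50 participants in each group will provide adequate power" for d = 0.50, with power 0.80 and one-tailed alpha 0.05. The 60 per group left after one-third attrition is then declared enough for every analysis.

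**The concern.** Youth who live together for one to three weeks share staff, peers, setting and year. The protocol presents peer interaction as one of the ways the program works, so by its own account outcomes within a session may be correlated. An ANCOVA with youth as independent units counts each as a full piece of information. If the session-level correlation is positive, this understates the standard error of every contrast between Group A and a comparator.

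The protocol recognises dependence by site but deals with it in a separate estimate that does not enter the treatment tests. That estimate also concerns three sites rather than the site-by-year groups in which youth are treated.

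At stake are the nominal 5% error rate and the stated power. The comparison most exposed is A versus C, because both arms are treated in groups. It is also the one meant to isolate the effect of the residential component.

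**Working it through.** **Inputs from the protocol article.** Three sites, one program per site each summer, three recruitment years. 90 enrolled and 60 retained per group. d = 0.50, one-sided alpha 0.05, power 0.80.

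**Assumptions, because the documents give no figure.** ICC of 0.02, 0.05 and 0.10; equal session sizes; nine program groups in C.

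**1. The plan's own figure.** n per group = 2(1.645 + 0.842)² / 0.50² = 49.5, so 50, with power 0.804. The figure is reproduced under independence, so it contains no allowance for clustering. At 60 per group, power under independence is 0.863.

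**2. Sessions.** 3 sites × 3 summers = 9 sessions in Group A. Retained youth per session: m = 60/9 = 6.7.

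**3. Design effect.** DE = 1 + (m − 1) × ICC. At ICC 0.05: 1 + 5.67 × 0.05 = 1.28.

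**4. Factor by which the correct standard error exceeds the assumed one.**
- Only A clustered (A versus B or D): f = √((DE + 1)/2).
- Both arms clustered (A versus C): f = √DE.

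**5. Error and power.** Actual one-sided error of the unadjusted test = 1 − Φ(1.645/f). Power of a test that uses the correct standard error = Φ(0.50/(f√(2/60)) − 1.645). Like the plan's own calculation, this is a single comparison of two means with no credit for baseline adjustment.

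| ICC | DE | f, A vs B or D | Error | Power | f, A vs C | Error | Power |
|---|---|---|---|---|---|---|---|
| 0 | 1.00 | 1.00 | 5.0% | 0.86 | 1.00 | 5.0% | 0.86 |
| 0.02 | 1.11 | 1.03 | 5.5% | 0.85 | 1.06 | 6.0% | 0.83 |
| 0.05 | 1.28 | 1.07 | 6.2% | 0.82 | 1.13 | 7.3% | 0.78 |
| 0.10 | 1.57 | 1.13 | 7.3% | 0.78 | 1.25 | 9.4% | 0.71 |

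With t reference distributions that reflect the number of clusters, power is a little lower. At ICC 0.05 it is 0.80 for A versus B or D and 0.75 for A versus C. At ICC 0.10 it is 0.76 and 0.67.

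**6. Precision of the three-site share.** There are 2 between-site degrees of freedom. The analysis-of-variance estimate of the share, (MSB − MSW)/(MSB + 19 MSW), was simulated for three sites of 20 youth (200,000 draws).
- True share 0.05: 95% of estimates lie between about −0.05 and 0.26, and 38% are zero or negative.
- True share 0.10: the range is about −0.05 to 0.37, and 27% are zero or negative.

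**The case against.** **No ICC is given, so the bias is not shown.** This stands. A reader might infer that the standard errors are certainly and materially too small. The documents support only the conditional statement: at ICC 0.01 with A alone clustered the understatement is about 1%, and at 0.02 under 3%.

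**Shared site effects may cancel.** Group B applied to the same programs, and Group D comes partly from the same three centres. A stable site effect common to both arms partly drops out of the contrast, and ignoring it could even be conservative. This stands for site effects. It does not cover the effect of a particular session, which B and D youth do not share.

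**The loss of power is modest.** Largely right for A versus B or D. A reader might divide 60 by 1.28, get an effective Group A size of 47 and call it short of 50. But the 50 applies to two equal groups and the comparator keeps its 60. The harmonic mean is 2/(1/46.8 + 1/60) = 52.6, and power is 0.82. Baseline adjustment would also recover some power: with an assumed baseline correlation of 0.3, power at ICC 0.10 is about 0.81 for A versus B or D. That does not repair the error rate.

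**The site share can be estimated.** True. A reader might infer that three sites give no estimate at all. They give one, but with the width shown above.

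**A condensed article leaves such detail to the full plan.** This would apply if the model were left open. The article instead names the primary model and its covariate, and assigns multilevel modelling to a different purpose.

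**Conclusion.** The point holds in conditional form. As stated, the primary tests and the sample size ignore the grouping that the intervention creates, and the multilevel step does not correct them. Under any positive session-level ICC, the contrasts of Group A with its comparators have standard errors that are too small.

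For ICCs of 0.02 to 0.10, the one-sided 5% error becomes about 5.5% to 7.3% against B or D, and about 6.0% to 9.4% against C. In the normal approximation, power falls below 0.80 above an ICC of about 0.075 for A versus B or D and about 0.038 for A versus C. The claim that 60 per group suffices for every analysis is therefore least secure for A versus C.

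These figures rest on assumed ICCs, nine equal sessions in A (inferred rather than stated), nine groups in C (assumed), and no gain from baseline adjustment. The three-site share is too imprecise to carry a conclusion.

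**What to change.** 1. Make the primary model a partially nested mixed model: a random effect for program session (site by year) in Group A and for program group in Group C, with B and D youth as singletons. Keep the baseline score as covariate. Use Satterthwaite or Kenward-Roger degrees of freedom.
2. In Statistical power, replace the statement that 60 per group is enough for every analysis by power over a stated range of ICCs, separately for A versus B or D and for A versus C, with the number of C groups given or assumed openly.
3. Label the three-site variance share as descriptive only.

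Cost: session or program-group membership must be recorded for each youth in A and C. Intervals become slightly wider and the stated power less favourable. No additional participants or assessments are needed.

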#### Qualitative analysis

Short debrief interviews from during the program, contemporaneous field notes, and verbatim transcripts of the in-depth interviews will form the data set for rigorous qualitative analysis, using NVivo for data management. This will provide an in-depth understanding of both parent and youth views of opportunities, experiences, and outcomes related to RILS versus non-residential life skills programs. The multidisciplinary team will play a key role in the synthesis and interpretation of the data [43]. Team members will read through each anonymised transcript several times and note emerging themes and patterns. Initial deductive codes related to opportunities, experiences, and outcomes will be identified. Inductive coding will then be used to identify other concepts that relate to the research questions. A list of themes will be generated then reviewed by multiple team members, refining and clarifying themes and categories iteratively. Dissenting views and ‘negative cases’ will be included. Once a final coding scheme has emerged, all documents will be re-coded by a single researcher. We will examine changes and correspondence of perceptions in the sets of parent and youth pre/post transcripts. An audit trail will be maintained to document methodological decisions and contextual notes [44]. Negative case analysis, debriefing sessions, and the involvement of expert team members who have familiarity with the participating programs will all enhance credibility, a key tenet of trustworthiness in qualitative research [45]. The triangulation of different data sources and identification of the team’s assumptions and beliefs will promote confirmability [46]. Although qualitative work aims to be conceptually generalizable rather than empirically generalizable [47], in-depth contextual information will be provided when reporting the qualitative study findings to enhance transferability [48].

#### Mixed-methods analysis

We will integrate quantitative and qualitative data at the level of interpretation. Qualitative and quantitative methodologies offer different strengths [49]. We will triangulate between complementary methods to increase the breadth and depth of our understanding of RILS programs [50]. We will examine qualitative themes addressing our overall objective of elucidating program opportunities, experiences, and outcomes. Profiles of MEQAS and SPS-C data will be examined in conjunction with qualitative themes concerning program opportunities; SEAS data will be examined in conjunction with qualitative themes concerning experiences; and links between these data and outcomes will be identified.

## Discussion

Our program of research and the longitudinal study that we have described in this protocol address key gaps in the literature relating to the long-term impact of RILS programs and the role of immersive environments (i.e., provided opportunities and youth experiences) in shaping youth outcomes. There is little existing research identifying the ‘key ingredients’ of RILS programs, programs that anecdotal evidence describes as being powerful ‘turning points’ in the lives of young people, their parents, and service providers [24, 27]. To our knowledge, this will be the first study to prospectively follow young people to examine changes in higher order life skills over time, comparing outcomes among youth in multiple control groups.

The research has significant implications for understanding how to optimally design and deliver RILS programs for youth with disabilities, through the exploration of program features and opportunities. Findings will make a unique contribution in the following ways: first, this theoretically grounded study will provide important new information about the fundamental processes by which RILS programs influence short-term and longer-term changes in youth. It is important to understand these processes because they are then potentially transportable to guide the development of effective programs for youth with disabilities, but also for other at-risk youth. Second, the research will explore the specific nature of the learning opportunities provided by these programs and how they impact youth experiences. Our understanding of the strategies used by service providers will also be extended from our earlier work [24]. Pilot work indicates that RILS programs accelerate the development of life skills, which will be further explored in this study. One of the strengths of the study is the use of reliable and valid measures of observable program features and intervention strategies. Our findings will support evidence-informed service not only in Ontario where the study RILS programs are based, but nationally and internationally, leading to improved life outcomes for youth with disabilities.

### Limitations

We aim to recruit youth who are dealing with a range of complex health conditions. As in any longitudinal study, there is the potential that some participants will withdraw, due to changing desires to participate, or be lost to follow-up. However, we have put in place incentives for participants to remain involved through the full 1-year period. The youth in the RILS group are involved in the highest number of research tasks; however, the most time-intensive period of research involvement occurs during the RILS programs, which is near the beginning of the 1-year period. This may help to minimise the number of youth who decide to withdraw. Baseline data will be retained for participants who withdraw, so that comparisons may be made between them and the youth who choose to remain involved.

### Ethics

Ethical approval has been obtained (see below for details). All youth, parents and service providers who are involved in the study will provide written informed consent to a research team member prior to the completion of any study activities. Identifying information for potential participants will be stored on an encrypted server, in a password protected folder. If the potential participant opts not to participate in the study, his/her identifying information will be deleted immediately. Identifying information for those who agree to participate in the study will be stored on the same encrypted server, in a password-protected folder that requires authorisation as a member of the research team. This information will be retained for the life of the study and will be used to provide participants with results of the study upon its completion.

